### ***Secondary endpoints***

- Number of participants who quit or reduced smoking at final follow-up.
- Number of participants who changed their eating pattern at final follow-up.
- Number of participants who quit or reduced alcohol consumption at final follow-up.
- Number of participants who increased their physical activity score
- Acceptability of the Polygenic Risk Score test for patients
- Acceptability of the pathway for both the hospital and patients.
- Compliance with the study, measured by the percentage of subjects who complete all follow-ups
- Compliance with interventions, measured by the number of subjects who adhere to the frequency, content, and duration of the proposed interventions

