## **METHODS**

### ***Study design***

Single-center, single-arm experimental study conducted on a cohort of subjects attending the A. Gemelli IRCCS University Hospital in Rome (Italy), enrolled at the outpatient clinics of the Cardiology Department.

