## DATA COLLECTION, RECORDING, AND STATISTICAL ANALYSIS

### *Questionnaire*

The study questionnaire is divided into several sections.

The lifestyle questionnaire (Life's Essential 8) will be administered at T0 and T2, and after completion, will provide a lifestyle score that will classify the patient into one of three categories (favorable, intermediate, unfavorable). The questionnaire has been validated on the European population and has already been used in several clinical studies. Its scale ranges from 0 to 100 [20].

It is divided into several sections, structured as follows:

**General lifestyle:** Smoking habits, alcohol consumption, physical activity, and amount of sleep

**Diet:** Types of foods included in one's diet

**Health factors:** BMI, cholesterol, blood pressure, and blood sugar

Questionnaire on personal and family history, socioeconomic and professional status, and demographic information, administered at T0. Questionnaire on the acceptability of the intervention to doctors and patients, administered at T2. Questionnaire on values and preferences regarding the use of new technologies [21], administered at T2. FACToR questionnaire, a revised version of the MICRA questionnaire, to assess the reaction to genetic testing [22][23], administered at T2.

At both T0 and T2, a questionnaire will be administered to assess anxiety levels (GAD-7) [24] and work status (Work Ability Index) [25].

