## **STATISTICAL ANALYSIS**

### **Sample calculation**

The study will be offered to all employees of the Policlinico Gemelli hospital who meet the inclusion criteria listed above ( ). It is estimated that out of a total of approximately 650 subjects who will be offered the intervention, 70% will participate in the project (N=455) and of these, 80% will complete the study (N=364). This sample size allows us to detect a mean difference of LE8 equal to 3 points (standard deviation=2) between the end and the beginning of the follow-up with a power greater than 90%.

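### The diet endpoint has no direction, and the activity, alcohol and (less so) smoking endpoints count only favourable movers, so in this single-arm study none of these counts can show net change

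*Protocol*

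**What the plan says.** The Secondary endpoints section of the Protocol lists four behavioural counts:

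- diet: "Number of participants who changed their eating pattern at final follow-up"
- activity: "Number of participants who increased their physical activity score"
- smoking: "Number of participants who quit or reduced smoking at final follow-up"
- alcohol: "Number of participants who quit or reduced alcohol consumption at final follow-up"

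The first has no direction. The other three have a favourable direction only. None has a minimum change or a matching count of those who got worse.

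Under Study design the trial is a "Single-center, single-arm experimental study conducted on a cohort of subjects", so there is no concurrent control. Under Questionnaire, "The lifestyle questionnaire (Life's Essential 8) will be administered at T0 and T2", and that instrument covers smoking, alcohol, activity and diet. The Statistical Analysis section plans mixed-effects models for lifestyle change. It does not say how these four counts are to be analysed or what they are to be compared with.

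**The concern.** People asked the same lifestyle questions some seven months apart give somewhat different answers even when their habits are stable. Some move up and some move down. A count of those who moved up cannot be negative and will be above zero whenever answers vary. A count of those who moved at all adds both directions together.

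In a controlled trial, the other arm would show how much of this movement is background. Here the only internal reference is the number who moved the opposite way. The endpoints as worded leave that number out or, for diet, merge it with the improvers.

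The counts also bear on the main question. The stated secondary objective is feasibility, whereas behaviour change belongs to the primary objective. Readers will therefore take a sizeable count as evidence that disclosing the PRS changed behaviour.

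**Working it through.** **Inputs from the Protocol.** The Sample calculation section gives 650 people offered the study, 70% participation and 80% completion. These reproduce: 650 × 0.70 = 455, and 455 × 0.80 = 364 completers. The Protocol states no expected value for any of the four counts, so there is no plan figure to reproduce for them.

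**Assumed inputs.** The Protocol gives neither the number of levels in the diet and activity scores nor their test-retest reliability. The check therefore takes 3, 5 or 7 equally filled categories and reliability *r* from 0.5 to 0.9, plus a continuous score for activity.

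**No-change reference.** Let *t* be the share with identical scores at T0 and T2. If the two visits are exchangeable,

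- P(up) = P(down) = (1 − *t*)/2
- P(changed) = 1 − *t*
- P(up) − P(down) = 0

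The share *t* was obtained by simulating 400,000 people with two exchangeable visits, and the results were scaled to 364. Each cell gives increased / changed in either direction:

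| *r* | 3 categories | 5 categories | 7 categories |
|---|---|---|---|
| 0.5 | 93 / 186 | 124 / 248 | 139 / 278 |
| 0.6 | 85 / 170 | 117 / 234 | 133 / 266 |
| 0.7 | 75 / 151 | 108 / 217 | 126 / 251 |
| 0.8 | 64 / 128 | 97 / 194 | 116 / 232 |
| 0.9 | 47 / 93 | 78 / 155 | 98 / 195 |

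- **Activity.** The lowest value is 47 (12.8%). A continuous score has no ties, so P(up) = 0.5 and 364 × 0.5 = 182. The range is 47 to 182, with as many moving down and not counted.
- **Diet.** The range for a categorical score is 93 (25.6%) to 278 (76.3%), and half of these are people whose diet score fell. A score with no ties would count all 364 as changed, so that case is left out of the range.
- **Ceiling effect.** With half the sample in the top category, 28.2% to 18.0% increase and 56.3% to 36.1% change, which lies inside the ranges above.
- **Smoking.** Only smokers can quit or reduce. If 10% to 30% smoke and 10% to 50% of them report less by chance (both assumed), the count runs from 364 × 0.10 × 0.10 ≈ 4 to 364 × 0.30 × 0.50 ≈ 55, or 1% to 15%.
- **Alcohol.** The same mechanism applies, but the share of drinkers is not given and no figure was computed.

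**What the net difference would show.** At zero net change, the standard error of improved minus worsened, as a proportion, is √(P(changed)/364). For P(changed) = 0.256 this is √(0.256/364) = 0.0265, so the 95% half-width is 1.96 × 0.0265 = 5.2 percentage points. For 0.763 it is √(0.763/364) = 0.0458, giving 9.0 points. The data to be collected can therefore give a usable net estimate.

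**The case against.** The strongest reply is that much of this is ordinary content of a statistical analysis plan, which is not at hand. Minimum changes, denominators, three-way tables and the choice of test often sit there. That stands for denominators and thresholds, whose absence from the Protocol is not an error. It does not cover direction. The Protocol itself fixes what each endpoint counts, and for diet that includes deterioration.

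Second, the main analysis already uses signed change: the LE8 score is a primary endpoint and mixed models are planned, so anyone who worsens pulls that estimate down. This stands, and it confines the problem to the secondary counts. It does not repair those counts.

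Third, context suggests that diet was meant to improve, since the T1 advice aims at fewer unhealthy behaviours and the neighbouring endpoints are all favourable. That is probably the intention, but the wording should say so.

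Fourth, the number who worsened is a fair reference only for symmetric error. This stands too. Regression to the mean, more favourable reporting at T2 and the written lifestyle advice at T1 could each make improved minus worsened positive with no effect of the PRS.

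A reader might also infer that all four endpoints will show many responders when nothing changes. The Protocol does not support that. Few can respond on smoking, alcohol was not quantified, and the figures for activity and diet rest on assumed reliability and granularity.

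**Conclusion.** The concern holds for how the four secondary endpoints are defined. The diet endpoint lacks a direction. The activity, alcohol and, to a lesser degree, smoking endpoints are one-sided counts that response variation alone makes positive and that cannot show net change.

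With no true change among 364 completers, the illustrative size is 47 to 182 for activity and 93 to 278 for diet. These are no-change reference values under symmetric variation, not forecasts. They move with the assumed number of categories and reliability.

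The problem does not reach the LE8 primary endpoint or the sample size. Nor does it follow that a net difference would measure the effect of PRS disclosure. It would remove symmetric measurement noise only. This is worth correcting before the results are tabulated, but it does not threaten the main analysis.

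**What to change.** 1. Reword the diet endpoint as the number of participants with an improved LE8 diet score at T2 compared with T0.
2. For each of the four behaviours, report improved, unchanged and worsened. Give the net difference (improved minus worsened) with a 95% CI. Use McNemar's test for binary states and a sign or Wilcoxon signed-rank test for ordered scores.
3. Report smoking and alcohol reduction among those who smoked or drank at T0, and show new starters separately.
4. State that the net difference removes symmetric measurement noise only, and does not separate the PRS effect from regression to the mean, reporting bias or the lifestyle advice given at T1.

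The cost is a few lines of endpoint wording and some extra table columns. The questionnaire is already given at T0 and T2, so no new data, visits or participants are needed.

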In light of this epidemic of cardiovascular disease, prevention becomes a fundamental objective for global healthcare systems. It is well known that improving one's eating habits, increasing physical activity, and quitting smoking reduce the risk of developing cardiovascular disease and, consequently, lead to a decreased burden in older age groups. [15,16]

The aim of this study is to encourage a healthy lifestyle in healthy individuals with low traditional cardiovascular risk by communicating their genetic predisposition risk profile, measured by calculating their PRS. This study would allow for the evaluation of innovative personalized approaches, with the ultimate goal of reducing the burden of future cardiovascular disease and the associated costs.

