### ***Primary objective***

- To evaluate the effectiveness of communicating the Polygenic Risk Score in modifying participants' lifestyle.

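### The secondary diet endpoint counts any change in eating pattern, without direction, so worsened and improved diets go into the same total

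*Protocol*

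**What the plan says.** The Protocol's Secondary endpoints section lists eight items, four of them counts of participants by behaviour:

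- Smoking: "Number of participants who quit or reduced smoking at final follow-up".
- Diet: "Number of participants who changed their eating pattern at final follow-up".
- Alcohol: "Number of participants who quit or reduced alcohol consumption at final follow-up".
- Physical activity: "Number of participants who increased their physical activity score".

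The Background and rationale section sets the purpose, "The aim of this study is to encourage a healthy lifestyle in healthy individuals with low traditional cardiovascular risk", and ties the expected benefit to "improving one's eating habits, increasing physical activity, and quitting smoking reduce the risk of developing cardiovascular disease". The Primary objective is worded neutrally: "To evaluate the effectiveness of communicating the Polygenic Risk Score in modifying participants' lifestyle".

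The Questionnaire section says that the Life's Essential 8 (LE8) questionnaire is given at T0 and T2 and is scored from 0 to 100. It describes the diet section only as "Types of foods included in one's diet". The Statistical Analysis section speaks of lifestyle and behavioural change in general and says nothing specific about the diet count.

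**The concern.** Three of the four behaviour endpoints can be read at sight: a larger number means that more people moved the desired way. The diet endpoint cannot. A participant who moves to a healthier diet and one who moves to a less healthy diet each add one to the same total. The rationale rests on diets improving, and a count that rises equally with improvement and deterioration does not measure that.

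This goes beyond detail left for later. The Protocol does fix a rule, and the rule gives a number with no interpretation as benefit. If a later document narrowed it to improvers only, the endpoint would differ from the one in the Protocol. If that happened after the data had been seen, it could be criticised as selective.

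**Working it through.** **Wording, side by side**

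| Behaviour | Verb in the endpoint | Direction stated? |
|---|---|---|
| Smoking | quit or reduced | yes, favourable |
| Alcohol | quit or reduced | yes, favourable |
| Physical activity | increased | yes, favourable |
| Diet | changed | no |

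The other places that could supply a direction do not. The Background speaks of improvement but does not define the endpoint. The Primary objective uses a neutral verb. The Procedures and Questionnaire sections describe collection of diet information at T0 and T2 without saying what counts as a change. The Statistical Analysis section does not mention the diet count.

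**Completers.** The Sample calculation section expects about 650 people to be offered the study, 70% to take part and 80% of those to complete it:

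- 650 × 0.70 = 455
- 455 × 0.80 = 364

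Both figures agree with the Protocol. It gives no expected figure for the diet endpoint.

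**What the count can and cannot show.** Let n be the completers, *p_i* the share whose diet improves and *p_w* the share whose diet worsens.

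- Endpoint as written: C = n × (*p_i* + *p_w*)
- Net movement: D = n × (*p_i* − *p_w*)

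C stays the same when *p_i* and *p_w* are swapped; D changes sign. With n = 364 and three pairs of assumed rates, chosen only for illustration:

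| Improve / worsen | Changed (C) | Improved | Worsened | Net (D) |
|---|---|---|---|---|
| 40% / 10% | 364 × 0.50 = 182 | 145.6 ≈ 146 | 36.4 ≈ 36 | 109.2 ≈ +109 |
| 25% / 25% | 364 × 0.50 = 182 | 91 | 91 | 0 |
| 10% / 40% | 364 × 0.50 = 182 | 36.4 ≈ 36 | 145.6 ≈ 146 | −109.2 ≈ −109 |

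The endpoint returns 182 in all three cases. A reported 182 would in fact fit any number of improvers from 0 to 182.

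**Reach.** The Sample calculation rests on a mean LE8 difference of 3 points with a standard deviation of 2. The diet count does not enter it, so no figure in the Protocol changes.

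**The case against.** The best defence is that the intended meaning is plain. The Background speaks of improving eating habits, participants receive written advice on reducing unhealthy behaviours, and the equally neutral verb in the Primary objective would not be taken to treat deterioration as success. On this view the word is merely loose. That is probably right about intention, but it does not mend the text: the context does not define the endpoint, and the neighbouring endpoints show that the Protocol states a direction when it wants one.

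A second defence is that the cut-off for calling someone changed is commonly left to the statistical analysis plan. That is accepted, and the absence of a threshold is no part of this point. The point is the word that the Protocol does fix.

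Three stronger readings may tempt a reader, and the document does not support them:

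- **The study could report harm as success.** This would need the diet count to be the study's main reading of diet. It is one of eight secondary endpoints. The primary LE8 change has a sign, and the questionnaire behind it has a diet section, so a worse diet pulls that score down. Gains in other sections may offset the fall, so the total is no substitute for a directed diet endpoint, but deterioration is not hidden from the study.
- **Reporting noise alone would produce a large count.** Any figure for this needs a number of diet groups and a test-retest correlation, and the Protocol gives neither. Noise also affects every count of responders, including the three directed ones, so it does not single out this endpoint.
- **A low genetic result could falsely reassure people and worsen their diet.** The Protocol contains no such argument, and the point does not need it.

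**Conclusion.** The point holds in a limited form. As written, the diet endpoint pools worsened with improved diets and cannot be read as benefit, unlike the three behaviour endpoints beside it. In the illustration, net effects of +109, 0 and −109 among 364 completers all appear as 182. The rates of improvement and worsening are assumptions; the lack of direction depends on none of them and follows from the wording alone.

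The consequence stays within one secondary endpoint. The primary LE8 analysis and the sample size are unaffected. The correction is worth making because the endpoint has no useful interpretation without it.

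**What to change.** Reword the endpoint along these lines:

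> Number and proportion of participants whose eating pattern improved from T0 to T2, based on the diet section of the LE8 questionnaire, with the number whose eating pattern worsened reported alongside.

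Showing both numbers matters because the study has a single arm: there is no control group against which to judge a count of improvers, and the number who worsened gives some context. The rule for classing a participant as improved or worsened can go in the statistical analysis plan, provided that it is fixed before the T2 data are seen. Making the mean change in a diet score the main diet analysis would be a matter of preference and is not needed to cure the defect.

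The cost is one sentence in the endpoint list. The questionnaire with its diet section is already completed at T0 and T2, so no visit, sample or instrument is added. The downside is that the headline count will be smaller than the undirected one whenever any participant's diet worsens: 146 instead of 182 in the first illustrative case.

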## **ENDPOINTS**

### ***Primary endpoint***

- Pre-post change in lifestyle score, measured using Life Essentials' 8, at baseline and at final follow-up [17,18,19,20]
- Changes in cardiovascular risk profile assessed using SCORE2 / SCORE2 OP

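### The activity, alcohol and smoking endpoints count only participants who improved, by any amount, so without a control group their expected value is well above zero for activity even when nothing has changed

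*Protocol*

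**What the plan says.** Under Secondary endpoints the protocol defines three behaviour outcomes as counts of people who improved: "Number of participants who increased their physical activity score", "Number of participants who quit or reduced alcohol consumption at final follow-up" and "Number of participants who quit or reduced smoking at final follow-up". No minimum size of change is given, and participants who moved in the unfavourable direction are not part of the definition.

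The Study design section describes a "Single-center, single-arm experimental study", so there is no comparison rate. The behaviours are self-reported twice: "The lifestyle questionnaire (Life's Essential 8) will be administered at T0 and T2". T2 falls six months after the disclosure visit (Procedures).

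Two other places treat change differently. The first primary endpoint is a "Pre-post change in lifestyle score, measured using Life Essentials' 8, at baseline and at final follow-up", which keeps both directions. The Statistical Analysis section plans adjusted mixed-effects models for repeated measures for changes in lifestyle. The Sample calculation section expects 364 completers.

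**The concern.** A mean change has a natural null value of zero. A count of improvers does not. If true behaviour is the same at T0 and T2 but each report carries some error, some people score higher the second time and about as many score lower. The endpoint as defined shows the first group and leaves out the second. With no control arm, nothing in the study tells a reader how many improvers to expect from noise alone.

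The stated primary objective is to evaluate how effective disclosure of the polygenic risk score is in modifying lifestyle, and these counts are its behaviour-by-behaviour results. A sizeable number of participants reported as having increased their activity after disclosure would be literally true with no effect, and could be true even if average activity fell.

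**Working it through.** **Inputs from the protocol.** 650 people approached, 70% taking part, 80% of those completing. 650 × 0.70 = 455, and 455 × 0.80 = 364, so the protocol's own figures reproduce. The power statement in the same section concerns the mean change in the Life's Essential 8 score and says nothing about these counts.

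**Assumptions, not in the protocol.** The number of grades in the activity score (3 to 8, equally filled), the retest correlation (0.6 to 0.9), the share of smokers, and the share of smokers who report less by chance.

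**Step 1: general relation.** With no true change and symmetric error, P(improved) = P(worsened) = (1 − P(unchanged)) / 2. The expected count is 364 times this.
- Nobody unchanged (continuous score): 0.50 × 364 = 182.
- 40% unchanged: 0.30 × 364 = 109.
- 60% unchanged: 0.20 × 364 = 73.
- 80% unchanged: 0.10 × 364 = 36.

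**Step 2: graded activity score.** Two bivariate normal readings of an unchanged trait, each cut at the same equally spaced quantiles:

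| Grades | Retest correlation | Increased | Decreased | Increased, of 364 |
|---|---|---|---|---|
| 3 | 0.9 | 12.9% | 12.9% | 47 |
| 3 | 0.6 | 23.3% | 23.3% | 85 |
| 5 | 0.9 | 21.4% | 21.4% | 78 |
| 5 | 0.6 | 32.1% | 32.1% | 117 |
| 8 | 0.9 | 28.9% | 28.9% | 105 |
| 8 | 0.6 | 38.0% | 38.0% | 138 |

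The range is about 13% to 38%, or 47 to 138 people, with an equal group worsening in every row.

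**Step 3: can the count look good while the mean falls?** Take 7 grades, correlation 0.6 and a true fall of 0.1 standard deviations. Then 32.6% (119 of 364) still increase, while 40.6% (148 of 364) decrease.

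**Step 4: smoking.** Only people who smoke at T0 can quit or cut down. At an assumed 10% to 30% smokers, that is 36 to 109 of 364. If 20% to 40% of them report less by chance, the count runs from 36.4 × 0.20 = 7 to 109.2 × 0.40 = 44. For alcohol the same limit applies to drinkers. The protocol gives no figure from which to size it.

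**Step 5: the net count.** Improved minus worsened has expectation zero under no change. Its standard error is √(2 × p × 364), where p is the share improving by chance. At p = 0.13 this is √94.6 = 9.7 people (2.7 percentage points). At p = 0.38 it is √276.6 = 16.6 people (4.6 points).

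**The case against.** Four arguments on the other side have weight.

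- **The sizes rest on assumptions.** The protocol gives 0 to 100 for the whole questionnaire and no grading for activity. A coarse score with good reliability brings the chance share down to 13%. This stands, which is why a range is shown. It does not bring the expected count to zero.
- **Graded, two-directional information is kept elsewhere.** The primary endpoint is a change in score and mixed models are planned. A reader might infer that counting improvers costs the trial a fixed share of its precision, or that the primary result is distorted in the same way. The documents support neither: the planned model uses the graded data, and the primary score change does not count in one direction only.
- **These are secondary counts with no success threshold, and tables and tests belong in a statistical analysis plan.** The first part stands and limits the severity. The second stands only for the choice of test. What is counted is fixed by the endpoint definition in the protocol.
- **The deeper problem is the missing control arm.** This stands. A net difference still could not be attributed to disclosure.

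A reader might also extend the point to all four behaviour endpoints. The wording does not allow it. The diet endpoint, "Number of participants who changed their eating pattern at final follow-up", names no direction, so a worsened diet would also be counted. That is a different weakness.

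**Conclusion.** The point holds for activity, alcohol and smoking. As defined, each is an improvement-only count with a non-zero expected value under no change and no reference to judge it by.

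For activity the chance count is substantial: about 47 to 138 of 364 completers under 3 to 8 equal grades and retest correlation 0.6 to 0.9, and up to 182 on a continuous score. An equal number would worsen without appearing in the endpoint. For alcohol a sizeable count is plausible but cannot be worked out from the document. For smoking the effect exists but is small in absolute terms, about 7 to 44 people under the assumed ranges, so calling all three counts large would go too far.

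The weakness lies in secondary endpoints and leaves the primary change score untouched. It should be corrected because it is cheap to do so before results are seen.

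**What to change.** - **Activity:** make the mean T0 to T2 change in the activity score, from the mixed model already planned, the main analysis. If the count of improvers is kept, show it as description beside those unchanged and those worsened.
- **Alcohol and smoking:** replace the one-directional count with three categories (improved, unchanged, worsened). Base inference on improved minus worsened, with a sign or McNemar test and a 95% confidence interval. Report quitting separately from reducing.
- **Limits:** state in the protocol that this removes symmetric reporting noise only. Without controls, regression to the mean, socially desirable reporting and secular trend remain, so a net improvement is not by itself evidence that disclosure caused it.

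The cost is a change in endpoint wording and a few extra table rows from data already collected at T0 and T2. The downside is that the headline counts will look less favourable.
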